### 2.10. Sample size

To calculate the number of subjects, the change in SPPB score, which measures muscle functionality, was used. The type I error rate (α) was 0.05, and the type II error rate (β) was 0.15; thus, the power of the test (1-β) was 85%. The effect size of the difference in the amount of change in SPPB score between the experimental and placebo comparator groups was assumed to be 0.6667. Due to the lack of previous clinical trials, a meaningful change in SPPB score to calculate the number of subjects was assumed to be 1.0.^[22]^ The coefficient of variance for the difference in the amount of change in SPPB score was assumed to be 1.5. Based on this information, 41 subjects were included in each group. Considering a dropout rate of 20%, 52 subjects in each group. Therefore, 104 subjects were required.

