### 2.11. Statistical analysis

The main analysis group for efficacy evaluation used the per-protocol set (PPS), which consisted of protocol-compliant subjects who completed the clinical trial. The secondary analysis group used the full analysis set based on the intention to treat that all subjects who have been randomly assigned should be the targets of the evaluation. Safety evaluation was performed on the safety analysis set, which included subjects whose safety information was collected more than once.

The significance level of the statistical analysis was set at 5% and a 2-tailed test was used. Continuous variables represent the number of participants, mean, and standard deviation. Categorical variables were presented as frequencies and percentages. The subjects’ demographic information, medication, and medical history presented the results of the PPS analysis group. To address missing full analysis set values, the last observation carried forward analysis was applied. To deal with the missing values of PPS and safety analysis set, the observed case approach, which analyzes missing values without correction, was used.

The mean, standard deviation, median, minimum value, and maximum value for the amount of change in the SPPB score, score for each SPPB item, hand grip, SMM, SMI, ASM, ASMI, BFM, %BF, FFM, TNF-α, IL-6, and IGF-1 are presented for each group. The least square mean (LSmean) and standard error of the amount of change corrected for the independent variable of the fitted general linear model are presented for each group. Comparisons between groups was analyzed by fitting a general linear model. If any factor affecting the outcome variable is identified, the general linear model is fitted by adding the factor as an independent variable. For data bias, the Wilcoxon rank-sum test, which is a non-parametric method, was applied. In addition, an analysis based on stratification factors was performed. Changes in the experimental or placebo comparator groups will be analyzed using a paired t-test or Wilcoxon signed-rank test.

The number of subjects with adverse events, drug adverse events, serious adverse events, incidence rate, 95% 2-tailed confidence interval, and the number of occurrences will be presented for each group. Differences in incidence rates between groups are analyzed using the chi-square test or Fisher’s exact test.

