In terms of laboratory tests, continuous data were presented as the mean and standard deviation for each group. Differences in the amount of change between the groups were analyzed using an unpaired *t* test (or Wilcoxon’s rank-sum test). Pre- and post-ingestion comparisons were analyzed using a paired *t* test (or Wilcoxon’s signed-rank test). Categorical data were presented as a shift table in terms of frequency and percentage. In addition, the comparison between pre-and post-ingestion will be analyzed using McNemar’s test.

In terms of vital signs, mean and standard deviation are presented for each group. The mean difference in the amount of change between groups was analyzed using an unpaired *t* test (or Wilcoxon’s rank-sum test). Pre- and post-ingestion comparisons were analyzed using a paired *t* test (or Wilcoxon’s signed-rank test).

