## 3. Discussion

EWGSOP defined grip strengths of <30 kg for men and 20 kg for women as cutoffs in the diagnostic criteria for sarcopenia, and AWGS defined grip strengths of <26 kg for men and 18 kg for women. We considered these criteria with respect to age when developing our inclusion criteria. For those aged 65 to 85 years, grip strengths of <26 kg for men and <18 kg for women were included.^[2,9]^

The incidence of sarcopenia has gradually increased due to a lack of physical activity and aging of the population. Unfortunately, sarcopenia may cause diseases, such as congestive heart failure or stroke. Additionally, it can lower quality of life. To treat sarcopenia, it is important to develop drugs for direct improvement, other than treatments such as regular exercise and a healthy diet, which are recommended in clinical practice.^[16]^

*C lanceolata* has shown positive changes in muscle.^[20,21]^ Therefore, this high-quality randomized controlled trial protocol was designed for a large-scale, double-blind clinical trial using *C lanceolata* water extract. This study is the first clinical trial of *C lanceolata* water extract in adults with reduced muscle strength. The results of this study would provide a clinical basis for the efficacy and safety of *C lanceolata* water extract in patients with sarcopenia, and this evidence will be useful to patients, doctors, and researchers. Through this study, we expect to see a reduction in diseases and disabilities caused by sarcopenia, and an improvement in ADL and quality of life.

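### The between-group safety comparison is planned as significance tests only, so no stated output shows how large an excess harm over placebo the data still allow

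*Protocol article*

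**What the plan says.** Section 2.11 of the protocol article gives the safety analysis in some detail.

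- **Adverse events, per arm.** For adverse events, drug adverse events and serious adverse events, the number of subjects affected is reported with "incidence rate, 95% 2-tailed confidence interval, and the number of occurrences will be presented for each group".
- **Adverse events, between arms.** "Differences in incidence rates between groups are analyzed using the chi-square test or Fisher’s exact test".
- **Laboratory values.** Each group is summarised by mean and SD. "Differences in the amount of change between the groups were analyzed using an unpaired" t test, or a Wilcoxon rank-sum test. Categorical results go into shift tables, with McNemar's test for the comparison before and after intake.
- **Vital signs.** Mean and SD per group, with the difference in mean change tested by the same pair of methods.
- **Level.** "The significance level of the statistical analysis was set at 5% and a 2-tailed test was used".

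Section 2.10 sizes the trial on efficacy alone: "To calculate the number of subjects, the change in SPPB score, which measures muscle functionality, was used". It arrives at 41 subjects per group, and 52 per group (104 in all) after allowing for 20% dropout.

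On the conclusion to be drawn, section 3 (Discussion) states: "The results of this study would provide a clinical basis for the efficacy and safety of" the extract in patients with sarcopenia. The Abstract carries the same statement.

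**The concern.** The stated conclusion and the stated outputs do not match. A clinical basis for safety requires knowing how much extra harm the product could cause relative to placebo. That takes an estimate of the difference and its upper confidence limit.

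The plan attaches its interval to each arm separately and gives the comparison only a p-value. An interval for one arm's incidence mixes the background rate with any product effect. A p-value does not separate a small, well-estimated difference from a large one that the trial was too small to detect.

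The trial was not sized for any safety comparison, so non-significant safety tests are likely for uncommon events even if the product does raise their frequency. This is described as the first clinical trial of the extract in this population, so later readers will depend on what it reports about harm.

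**Working it through.** **1. The plan's own figure.** Inputs from section 2.10: difference 1.0, SD 1.5 (the article calls it a coefficient of variance; the effect size of 0.6667 equals 1.0/1.5), α = 0.05, power 85%. Section 2.11 specifies two-sided testing.

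n per arm = 2 × (1.960 + 1.036)² / 0.6667² = 40.4, rounded up to 41. With 20% dropout, 41 / 0.80 = 51.25, rounded up to 52. The 41, 52 and 104 all reproduce. The calculation concerns the SPPB only.

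**2. Power of the adverse-event tests.** The safety set holds at most 52 per arm. The article gives no adverse-event rate, so placebo rates are assumed over a range. Power is the sum, over all pairs of counts (a, b) from 0 to 52, of Bin(a; 52, p0) × Bin(b; 52, p1) for those pairs where the test gives two-sided p < 0.05. Fisher's exact test and the uncorrected chi-square test were enumerated separately.

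| Placebo | Product | Ratio | Power, Fisher | Power, chi-square |
|---|---|---|---|---|
| 5% | 10% | 2 | 7% | 15% |
| 10% | 20% | 2 | 21% | 29% |
| 15% | 30% | 2 | 37% | 46% |
| 20% | 40% | 2 | 52% | 62% |
| 30% | 60% | 2 | 85% | 90% |
| 5% | 15% | 3 | 26% | 40% |
| 10% | 30% | 3 | 67% | 75% |
| 15% | 45% | 3 | 90% | 93% |

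A doubling is missed more often than not at placebo rates up to 15%, and detected more often than not from 20%. A tripling is usually missed at 5%, but not at 10%.

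**3. Laboratory values and vital signs.** For an assumed shift of 0.5 SD, the two-sided t test has 71% power at 52 per arm and 61% at 41 per arm. Such a shift would more often be found than missed.

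**4. What a difference with an interval would add.** Take 10/52 events on product and 5/52 on placebo, a doubling.

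- Incidence: 10/52 = 19.2%, 5/52 = 9.6%; difference 9.6 points.
- Wilson 95% limits: 10.8% to 31.9% (product) and 4.2% to 20.6% (placebo).
- Newcombe lower limit: 9.6 - √[(19.2 - 10.8)² + (20.6 - 9.6)²] = -4.2 points.
- Newcombe upper limit: 9.6 + √[(31.9 - 19.2)² + (9.6 - 4.2)²] = +23.4 points.
- Fisher p = 0.26; uncorrected chi-square p = 0.16.

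The planned tables would show the two incidences, their separate intervals and a non-significant p-value. They would not show that an excess of up to 23 points remains possible. Even with 5/52 in both arms (p = 1.0), the interval is -12.3 to +12.3 points.

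**The case against.** The case on the other side has real force.

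- **No rule equates non-significance with safety.** A reader might infer that safety will be concluded from p > 0.05. The article does not say so. The safety wording in the Abstract and Discussion is a general expectation, and the inference should not be charged to the plan.
- **Some confidence bounds are planned.** It would be wrong to say that the safety analysis has none: each arm's incidence gets a two-sided 95% interval. What is absent is an interval for the difference.
- **Other safety information is planned.** There are shift tables, comparisons before and after intake, severity grading and causality classification (section 2.12). From the published counts, means and SDs a reader could work out a difference and an approximate interval.
- **The tests are not blind to every large harm.** A reader might infer that they usually miss any doubling or tripling, or that a laboratory shift would probably go unnoticed. The power figures above do not support this. Nor would 10/52 against 3/52 show a missed harm: Fisher gives p = 0.072, but uncorrected chi-square gives p = 0.038, so the result depends on which of the two named tests is used.
- **Convention.** A safety margin, or a sample size based on adverse events, is not normally expected in an efficacy trial of 104 people. A condensed article may leave some table content to a fuller document.

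These points limit the size of the criticism but leave its core. The article does not merely stay silent. It specifies the interval, its sidedness and where it applies (each group), and it specifies a test for the comparison. That stated choice leaves the quantity most relevant to the safety conclusion unreported.

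**Conclusion.** The point holds as a modest, inexpensive improvement to the stated analysis; it is not an error that invalidates it. Section 2.11 compares safety between groups only by significance tests and places its 95% interval on each arm, so the excess harm still compatible with the data is not among the stated outputs, although the article expects to give a clinical basis for safety.

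The practical weight depends on the background adverse-event rate, which the article does not give. It is greatest for uncommon events: below a placebo rate of about 20%, a doubling would more often than not come out non-significant. For common events, or a tripling from 10% or more, the tests usually detect the difference. All these figures assume a safety set of 52 per arm and a two-sided 5% level; a smaller set would lower them.

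**What to change.** In section 2.11:

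- For adverse events, drug adverse events and serious adverse events, report the risk difference (product minus placebo) with a 95% confidence interval, for example Newcombe's.
- For laboratory values and vital signs, report the between-group mean difference in change with a 95% confidence interval.
- State that a non-significant safety test will not be taken as evidence of safety.

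The planned tests and per-arm summaries can stay alongside.

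In the Abstract and Discussion, word the safety conclusion as descriptive and give the upper confidence limit of the excess.

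The cost is a few table columns and some rewording. No safety margin, new data or additional patients are needed. The downside for the sponsor is a less favourable safety statement, because the upper limits will be wide at this sample size.

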##### 2.9.2.6. Adverse events

The researcher will evaluate adverse events at the sixth and 12th week visits through non-directive questioning of participants. The participants may have voluntarily reported any adverse events. Physical tests, laboratory tests, and other assessments can be performed to identify adverse events.

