##### 2.9.2.7. Laboratory tests and vital signs

Hematologic examination, blood chemistry examination, and urinalysis tests are performed at screening and at the 12th week of visits. Systolic blood pressure, diastolic blood pressure, pulse, and body temperature were measured at the screening, baseline, and both subsequent visits. Blood pressure and pulse were measured using the same FT-500R PLUS automatic blood pressure monitor (Jawon Medical Co. Ltd., Gyeongsan, Republic of Korea) after a 10 minutes rest.

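### The only test named for categorical laboratory shifts is a pre/post McNemar test, which makes no comparison with placebo

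*Protocol article*

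**What the plan says.** All the analysis statements are in section 2.11 of the protocol article.

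- **Categorical laboratory data.** "Categorical data were presented as a shift table in terms of frequency and percentage". The next sentence adds that "the comparison between pre-and post-ingestion will be analyzed using McNemar" (McNemar's test). No other test is named for these data.
- **Continuous laboratory data.** "Differences in the amount of change between the groups were analyzed using an unpaired" t test, with the rank-sum test as alternative. A paired pre/post test is planned as well.
- **Vital signs.** The same pair of analyses: change compared between groups, and a paired pre/post test.
- **Adverse events.** "Differences in incidence rates between groups are analyzed using the chi-square test or Fisher" (Fisher's exact test).
- **Level.** "The significance level of the statistical analysis was set at 5% and a 2-tailed test was used".

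Section 2.9.2.7 fixes the timing: "Hematologic examination, blood chemistry examination, and urinalysis tests are performed at screening and at the 12th week of visits". Each subject therefore has one value before and one after the product. Section 2.9.2.6 adds that "Physical tests, laboratory tests, and other assessments can be performed to identify adverse events".

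**The concern.** McNemar's test asks whether, in one set of subjects, more move from normal to abnormal than the other way. It uses only the subjects who changed category, and the randomised group does not enter. With one value at screening and one at week 12, the pre/post change mixes any product effect with time, assay changes and regression to the mean. Some drift is plausible here, because section 2.3.2 screens out high creatinine, AST/ALT and HbA1c values, so a few subjects admitted just inside a limit may cross it later in either arm.

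Two errors follow. Drift shared by both arms can look like a safety signal, and a real excess over placebo can be hidden when other subjects in the active arm return to normal. Categorical laboratory data are the only safety item in section 2.11 without a between-group test, in a placebo-controlled trial that is meant to inform on safety as well as efficacy.

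**Working it through.** **Inputs from the article.** Section 2.10 gives 41 per group before dropout and 52 after 20% dropout. Section 2.11 gives a two-sided 5% level. Section 2.9.2.7 gives one laboratory value before and one after.

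**The plan's own figures.** No figure in the article bears directly on this point. The group sizes used below do reproduce. With a difference of 1.0, SD 1.5, two-sided 5% and 85% power, n = 2 × (1.960 + 1.036)² × 1.5² / 1.0² = 40.4, so 41. Then 41 / 0.80 = 51.25, so 52 per group and 104 in all.

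**Assumptions.** The article gives no shift rates, so all rates and counts below are assumed, for a single laboratory parameter. The exact form of McNemar's test is also assumed.

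**Formula.** Let b be the number going from normal to abnormal and c the number going back, with k = b + c. The exact two-sided p-value is 2 × Σ C(k, j) / 2^k, summed over j from max(b, c) to k and capped at 1.

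**1. Same drift in both arms, no product effect.** Let s be the probability that McNemar is significant in one arm. As the arms are independent and identical, the probability of active significant and placebo not is s(1 − s).

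| To abnormal / back to normal | 52 per arm: active significant | 52 per arm: active only | 41 per arm: active significant | 41 per arm: active only |
|---|---|---|---|---|
| 20% / 4% | 59% | 24% | 45% | 25% |
| 15% / 3% | 42% | 24% | 29% | 21% |
| 10% / 2% | 21% | 17% | 12% | 11% |
| 10% / 6% | 5% | 5% | 4% | 3% |
| 5% / 1% | 3% | 3% | 1% | 1% |
| 10% / 10% | 2% | 2% | 2% | 2% |

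Check on the first row: 0.589 × (1 − 0.589) = 0.242.

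**2. A false signal in counts.** Suppose each arm of 52 has b = 8 and c = 1. McNemar gives 2 × (9 + 1) / 512 = 0.039 in each arm. Fisher's exact test between arms, 8/52 against 8/52, gives p = 1.0.

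**3. A missed signal in counts.** Suppose the active arm has b = 7 and c = 3, and no placebo subject becomes abnormal. McNemar in the active arm gives 2 × (120 + 45 + 10 + 1) / 1024 = 0.34. Fisher on new abnormalities, 7/52 against 0/52, gives p = 0.013. The three who returned to normal cannot be newly abnormal, so at most 52 − 3 = 49 active subjects are at risk. With 7/49 against 0/49, Fisher gives p = 0.012, so the choice of denominator does not alter the contrast.

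**The case against.** A reader might infer that the placebo arm is not used at all to judge laboratory abnormalities. The article does not support that. Change in continuous laboratory values is compared with placebo. So is adverse event incidence, and an abnormality recorded as an adverse event reaches that comparison. These routes are incomplete, however. A comparison of means does not cover urinalysis categories and can miss a few subjects crossing a limit, and section 2.9.2.6 does not say that every abnormal shift is recorded as an adverse event.

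A reader might also extend the point to efficacy, because "Changes in the experimental or placebo comparator groups will be analyzed using a paired t-test or Wilcoxon signed-rank test". That does not follow. Section 2.11 compares groups with a general linear model, and nothing rests an efficacy claim on one arm being significant and the other not. Leaving out the supplementary within-group p-values would be a matter of preference.

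Three further objections carry weight:

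- **Reading.** The article does not say outright that McNemar is applied within each group, or that the shift table is by group. Both are likely, and a table by group would allow a descriptive comparison. The only named inference would still ignore placebo.
- **Condensed text.** The full protocol or an analysis plan may add a between-group comparison. But the article does not leave the choice of test open: it names one, and that one does not fit the question.
- **Size.** The large false-signal rates need worsening to outnumber improvement about 5 to 1 and shifts to be fairly common. When shifts are rare or nearly balanced, the rate is about 1% to 5%.

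The remedy also has limited power. At 52 per arm Fisher gives p = 0.057 for 5 against 0 and p = 0.11 for 6 against 1, and power for 10% against 2% is about 21%. The risk difference with its interval is therefore worth more than the p-value.

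**Conclusion.** The point holds in a narrow form: the one test named for categorical laboratory shifts carries no treatment contrast, while the neighbouring safety measures each have one. With equal drift and no product effect, the chance of a significant result in the active arm is about 1% to 59% over the assumed rates and the two group sizes. The upper end needs 20%/4% shifts and 52 per arm. The count examples show that the test can err in both directions, but they are illustrations and not forecasts. The point is minor, since it concerns one secondary safety summary.

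**What to change.** In the laboratory paragraph of section 2.11:

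1. State that the shift table is presented by group.
2. For each categorical parameter, compare between groups the proportion newly abnormal at week 12 among subjects normal at screening, with the risk difference, its 95% confidence interval and Fisher's exact test.
3. Keep McNemar's test only if it is labelled descriptive.

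This takes a sentence or two of text and a little programming. It needs no new data and matches the plan's own handling of adverse events. The cost is a few more low-powered safety comparisons, which should themselves be read as descriptive.

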### 2.12. Adverse events

Subjects will be assessed for any adverse events during their visits and/or investigation. If a serious adverse event occurs, appropriate tests and follow-ups should be performed to prevent unnecessary risk. In addition, the principal investigator or researcher should notify the monitor and report to the IRB on the SOP of the institution. All adverse events must be reported for eCRF. If any necessary risk occurs to the subject, compensation should be made in accordance with the rules for compensation for damage.

The severity of adverse events was evaluated as mild, moderate, or severe, based on the maximum intensity. Causal relationships with products for clinical trials were classified into 6 categories according to the World Health Organization Uppsala Monitoring Center criteria.

### 2.13. Stopping rules

Subjects may withdraw consent at any time for any reason without a disadvantage. In addition, a subject may withdraw for any reason. Subjects who discontinued the trial will complete the efficacy and safety assessments, with the exception of declining revisits.

Subjects may be withdrawn by the researcher if: a violation of the inclusion/exclusion criteria is found during the clinical trial; the clinical trial is discontinued due to a sudden accident; their safety might be compromised for any reason; a serious adverse event including excessive predicted symptoms or death occurs; they take contraindicated drugs or the researcher assesses whether the subject requires any treatment with contraindicated drugs; the researcher assessed that they were no longer able to participate in the study due to inappropriate dosing of IP; the subject is lost to follow up; they suffer a worsening of symptoms; and if researcher assesses they are no longer able to participate due to other reasons. The subject may withdraw from or discontinue the study if they or a legal representative withdraws consent, if they suffer an adverse event, or any other reason, such as their refusal to consume the IP or non-cooperation.

This clinical trial may be prematurely terminated at the subject’s request, the occurrence of an adverse event, serious protocol violation, or other plausible reasons. The principal investigator has the final authority to discontinue or modify a clinical trial. In this case, the principal investigator promptly notifies the monitor by phone or by writing.

